### Suicide risk monitoring

All participants receive an information brochure with all relevant contact information as part of the information package they receive prior to the study. In addition, the brief version of the PHQ-9, the PHQ-4^44^ is administered before each treatment session or weekly via email (CAU). Suicide risk is monitored with the help of a suicide risk protocol that was created specifically for this study ([name] *et al Suicide protocol)*. Suicide risk is monitored using item 3 (‘feeling down, depressed or hopeless’) of the PHQ-4 and item 9 (‘thought that you would be better off dead, or of hurting yourself’) of the Beck Depression Inventory scale.^45^ If deemed necessary, participants are called and referred to appropriate services, including their General Practitioner (GP) or 113zelfmoordpreventie (online platform for suicide prevention). In addition, the participant also receives a pop-up message on the questionnaire page with relevant contact information right after filling in the questionnaire (ie, where they can find help if needed with relevant contact information).

### Assessments

The RCT includes five assessment points: (1) a baseline assessment including a diagnostic interview and questionnaires, (2) a midtreatment questionnaire, 5 weeks after baseline, (3) a post-treatment questionnaire, 8 weeks after baseline and (4) follow-up measurements, 6 months and (5) 12 months after baseline (figure 1). In addition, prior to each treatment session, or weekly in the CAU condition, participants fill out a short online questionnaire. This questionnaire briefly assesses symptom severity and monitors suicidal ideation.

**Figure 1 F1:**
[figure not shown]
Flow of the study.

### Primary outcomes

The Generalised Anxiety disorder-7 (GAD-7)^35^ and the Patient Health Questionnaire-9 (PHQ-9)^46^ are the primary outcomes in the study and assess respectively *anxiety and depressive symptoms* on a continuous scale. The 7-item GAD is a self-report questionnaire measuring anxiety symptoms. All items are scored on a scale from 0 (‘not at all’) to 3 (‘nearly every day’), with total scores ranging from 0 to 21. A higher score on the questionnaire is associated with a more severe experience of anxiety symptoms. The GAD-7 questionnaire has good psychometric properties including a good test retest reliability (ICC=0.83)^35^ and a good internal consistency (o.79<α<0.91).^47^ The PHQ-9 questionnaire is used to screen for self-reported symptoms of depression. The nine items are scored on a 0–3 scale, resulting in a total score between 0 and 27. A higher score on the scale indicates a more severe experience of depressive symptoms. The PHQ-9 is a valid and reliable tool with good sensitivity (0.88) and high specificity (0.94)^48 49^ (see table 1 for an overview of all questionnaires on all time points).

**Table 1 T1:** Overview of the measures separately for each assessment point

	Questionnaire	Assessment points					
		Baseline (t1)	Presessions	Midtreatment (t2)	Post-treatment (t3)	6 months follow-up (t4)	12 months follow-up (t5)
Anxiety	GAD-7	X	X*	X	X	X	X
Depression	PHQ-9	X	X*	X	X	X	X
Social anxiety	SIAS-6	X		X	X	X	X
Social anxiety	Mini-SPIN	X	X	X	X	X	X
Alcohol use	AUDIT-C	X		X	X	X	X
Drug use	DAST-10	X		X	X	X	X
Quality of life	EQ-5D	X			X	X	X
Objective academic achievement	†	X			X	X	X
Subjective academic achievement	PSS-WIS	X			X	X	X
Perfectionism	DEQ-SCP (short)	X					
Suicide risk	BDI-II (item 9) PHQ-4 (item 3)		X				
Medical service use	TiC-P				X	X	X
Satisfaction with intervention	CSQ-8				X		

*PHQ-4, brief anxiety and depression measure to monitor symptoms.

†Self-developed questionnaire.

AUDIT-C, Alcohol Use Disorders Identification Test-Concise; BDI-II, Beck Depression Inventory scale –II; CSQ-8, Client Satisfaction Questionnaire—eight items; DAST-10, Drug Abuse Screening Test—ten items; DEQ-SCP, Depressive Experiences Questionnaire - Self-Critical Perfectionism; ECS-R-SF, Revised Experiences in Close Relationships—Short Form; EQ-5D-5L, EuroQol-5D-5L; GAD-7, General Anxiety Disorder-seven items; Mini-SPIN, Mini-Social Phobia Inventory; PHQ-4, Patient Health Questionnaire—four items; PHQ-9, Patient Health Questionnaire-nine items; PSS-WIS, Presenteeism Scale for Students—Work Impairment Scale; SIAS-6, Social Interaction Anxiety Scale—six items; TiC-P, Treatment Inventory of Costs in Patients.

### Secondary outcomes

*Alcohol* and *drug use* are measured with respectively the Alcohol Use Disorders Identification Test-Concise (AUDIT-C)^50 51^ and the Drug Abuse Screening Test – 10 items (DAST-10).^52^ The AUDIT-C is a brief screening tool for identifying early and/or heavy alcohol use. The scale consists of 3 items, all scored on a 0–4 scale, resulting in a total score ranging from 0 to 12. The DAST-10 consists of 10 items. Item responses are ‘yes’ or ‘no’. Higher scores indicate a more severe level of drug abuse problems. The DAST-10 reports high validity (α=0.94) and reliability in a broad range of settings and populations.^53^

*Quality of life* is measured with the EuroQol-5D-5L scale (EQ-5D-5L).^54^ The EQ-5D-5L assesses health-related well-being on five dimensions: mobility, self-care, ordinary activities, discomfort and mood state. The sixth item of the EQ-5D-5L is a VAS scale, ranging from 0 to 100, asking the participant to rate their health perception at that moment. The EQ-5D-5L has high levels of acceptability and sensitivity.^55 56^

*Academic achievement* is measured with objective and subjective measures. Students are asked to report their number of European Credit Transfer System as an objective measure of their academic performance. Additionally, the work impairment subscale of the Presenteeism Scale for Students (PSS-WIS)^57^ is administered to assess subjective academic achievement on a 5-point Likert scale ranging from ‘always’ (0) to ‘never’ (5). The PSS-WIS is a valid (ICC=0.88 (95% CI p<0.001)) and reliable (test–retest reliability r=0.80, p<0.001) self-report measure to screen for impaired work performance due to (mental) health problems.^57^

*Medical service use* is measured with two items from the Treatment Inventory of Costs in Patients with mental disorders.^58^ The first item includes the frequency of contact with conventional care services (eg, general practitioner, study advisor, psychologist, medical specialist). The second item includes the use of medication during the length of the treatment period.

*Client satisfaction with treatment* is measured with the Client Satisfaction Questionnaire—eight items (CSQ-8).^59 60^ The CSQ-8 consists of 8 items scored on a 1 (‘quite dissatisfied’) to 4 (‘very satisfied’) scale, with total scores ranging between 8 and 32. The CSQ-8 is a standardised satisfaction measure reporting very good internal consistency (α=0.83–0.93) and high validity.^61^

Finally, following previous studies (for a systematic review), 62
*treatment adherence* is measured by tracking the activities in Minddistrict. We collect the total number of modules completed, time spent per module and the number of times the participants log into the Minddistrict platform.

### Predictors of treatment outcome

*Social anxiety* is measured with the Social Interaction Anxiety Scale-6 item (SIAS-6)^63^ and the brief Mini-Social Phobia Inventory (Mini-SPIN).^64^ The brief Mini-SPIN^64^ is included to screen for generalised social anxiety disorder. The scale shows strong sensitivity (93.8%) and good internal consistency (α=0.85).^65 66^ Besides the administration on t1–t5, the Mini-SPIN is administered before each treatment session, or weekly via email (CAU), to monitor the social anxiety status of the participant.

*Perfectionism* is measured with the short version of the Self-Critical Perfectionism subscale of the Depressive Experiences Questionnaire (DEQ-SCP).^67^ The subscale consists of 12 items. The DEQ-SCP scale is a simple, valid scale demonstrating good psychometric properties, in both clinical and student samples.^68^

Besides the inclusion of social anxiety and perfectionism, we include several variables to study possible predictors of treatment outcome including demographic variables (ie, age, gender, study direction, faculty, national/international student), baseline severity, personality factors, number of sessions completed/adherence rate and comorbidity for explorative analyses.

### Statistical analyses

#### Sample size calculation

The power analysis is based on the mixed factors 3×3 interaction difference between the three treatment arms and three time points (premeasurement, midmeasurement and postmeasurement). We anticipate a small interaction effect (Cohen’s f=0.1) at post-treatment based on a recent meta-analysis that focused on the effectiveness of therapist-guided versus computer-guided psychotherapy in treating depression and anxiety.^17^ We determined a statistical power (1-ß) of.8 and corrected alpha of α=0.05. With a two-tailed hypothesis, we need 204 participants per intervention group to be able to detect a statistically significant result. Previous literature has shown that web-based interventions have a relatively high reported range of drop-out in university students, varying between approximately 30% and 40% posttreatment.^20^ Calculating with a dropout rate of 35%, the minimum required total sample for the RCT is N_total_=276 participants (with a ratio of 1:1:1), with 92 participants in each group.

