Several studies demonstrated that the effectiveness of guided internet-based cognitive behavioural therapy (iCBT) programmes for anxiety and depression is comparable to conventional (face-to-face) CBT (for meta-analyses, see Carlbring *et al* and Cuijpers *et al*^16 17^). There is also some evidence for the effectiveness of internet interventions for young adults and university student populations with various mental health problems, including depression, anxiety, eating disorders, stress, alcohol and sleep problems^18–22^. For example, a recent meta-analysis^20^ focused on university students with mental problems, who self-selected a psychological online intervention (guided/unguided). They found small intervention effects for depression (*g*=0.18, 95% CI (0.08 to 0.27) and anxiety (*g*=0.27, 95% CI (0.13 to 0.40)) in university students. It should be noted, however, that the effects on anxiety were not significant anymore after adjusting for publication bias. Harrer and colleagues^20^ concluded that clearly more research is needed to explore ways to increase treatment effectiveness for university students and to study predictors of treatment outcome.

The current study includes a group of university students and focuses on two of the most common mental disorders in this group, namely, anxiety and depression.^2^ As comorbidity is high, we will use a transdiagnostic iCBT intervention, which has the advantage to target both disorders at the same time and thereby might increase treatment effectiveness (for a systemic review and meta-analysis, see Newby *et al*

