23). Moreover, iCBT programmes can be provided with or without additional personal guidance. Guidance usually implies written or verbal feedback by the therapist to the patient’s homework assignments and other forms of (safe) communication (eg, chat, telephone) within an online environment with varying degrees of interactive features.^24^ Both approaches (with and without personal guidance) have shown to be efficacious, although programmes with (therapist) guidance generally report a higher effect size (for meta-analyses, see Cuijpers *et al* and Richards and Richardson 17 25), even though it should be noted that a recent meta-analysis^20^ found no difference between personal or no personal guidance. To date, little is known about the effectiveness for therapist-guided versus a computer-guided version of the same intervention tested *within* the same study when applied to a university student sample with mental health concerns^20 26 27^. This could also have important health economic implications considering the additional cost of human support. Therefore, the current study tests this transdiagnostic iCBT for anxiety and depression in three groups; a therapist-guided online self-help version, a computer-guided version of the same programme and care as usual (CAU). Primary outcomes were anxiety and depression; secondary measures were included to evaluate treatment adherence and satisfaction, academic achievement and medical service use.

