Internet-based programmes, either therapist-guided with personal feedback or computer-guided with automated feedback, might suit some individuals better than others. It is important to focus on possible treatment predictors (eg, including baseline symptoms severity, gender, personality factors and comorbidity), as this may help us understand more about the heterogeneity of treatment response.^20 28^ Specially, a recent meta-analysis^20^ found limited effectiveness on anxiety in university students in their meta-analysis. The current study will focus on the possible role of social anxiety and perfectionism, as there is some evidence that adults and children with social anxiety might benefit less from general CBT programmes (for meta-analyses, see Hudson *et al* and Norton and Price^29 30^). Likewise, self-critical perfectionism is a transdiagnostic personality factor that is generally associated with worse treatment outcome, including CBT.^31^ Importantly, individuals with self-critical perfectionism have poorer social relationships, which in turn negatively impacts therapeutic progress.^32^

The aim of this study is to test the effectiveness of a therapist-guided versus a computer-guided transdiagnostic iCBT programme with a focus on anxiety and depression. Based on previous studies in the general population,^17^ we hypothesise that the therapist-guided iCBT and computer-guided iCBT conditions are both significantly more effective than CAU. In addition, we expect that the therapist-guided iCBT condition is significantly more effective than the computer-guided iCBT condition; an effect we expect to be mediated by higher treatment adherence.

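### The stated 80% power covers only the omnibus 3×3 interaction; the three hypothesised pairwise contrasts have no stated power, and the two between neighbouring arms would fall well short of 80%

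*Protocol article*

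**What the plan says.** The end of the Background sets out the hypotheses. Both iCBT arms are expected to beat CAU and, in addition, "we expect that the therapist-guided iCBT condition is significantly more effective than the computer-guided iCBT condition". These are three pairwise, directional statements.

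The Sample size calculation section powers a different test: "The power analysis is based on the mixed factors 3×3 interaction difference between the three treatment arms and three time points". On the effect size it says: "We anticipate a small interaction effect (Cohen’s f=0.1) at post-treatment". The same sentence gives the source, placing the effect "at post-treatment based on a recent meta-analysis that focused on the effectiveness of therapist-guided versus computer-guided psychotherapy in treating depression and anxiety", which is a two-arm comparison. Power and significance level follow: "We determined a statistical power (1-ß) of.8" and "corrected alpha of α=0.05". The section then arrives at 204 participants (labelled per group), allows for 35% dropout and ends with 276 in total, 92 per arm. It gives no power or detectable difference for any pairwise contrast.

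The closing paragraph of the Discussion presents the therapist-versus-computer comparison in a large sample as what makes the trial unique.

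**The concern.** A 4-df interaction test asks whether the three arms follow different courses over three time points. Rejecting it does not show which arms differ, so 80% power for it is not 80% power for any of the three hypotheses.

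The effect size adds to the difficulty. A reader who sees a small f tied to a therapist-versus-computer meta-analysis will take the trial to be sized for a small difference between those two arms. In this calculation f is instead the root mean square of the interaction cell effects, averaged over nine arm-by-time cells. An f of 0.1 on that scale corresponds to a much larger gap between the extreme arms than the word small suggests.

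What is at stake is how the results are read. If a pairwise contrast is not significant, the published 80% will make that look more informative than it is. The Background ties the therapist-versus-computer question to the cost of human support.

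**Working it through.** **Inputs from the protocol:** 3 arms, 3 time points, f=0.1, alpha 0.05, power 0.8, 35% dropout, 276 randomised (92 per arm).

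**Assumptions not in the protocol:** correlation between measurements rho=0.5; sphericity; for the pairwise checks, a two-sided 0.05 test at t3, either unadjusted (SD 1) or baseline-adjusted (SD √(1−rho²)); d=0.2 as one reading of a small pairwise effect.

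**1. Reproduce the plan's figure.** For a within-between interaction, lambda = f²·N·m/(1−rho), df1 = (3−1)(3−1) = 4, df2 = (N−3)·2. With N=204: lambda = 0.01×204×3/0.5 = 12.24, df2 = 402, power 80.6%. With N=201, power is 79.9%, so 204 is the smallest equal-arm total. Other correlations give different equal-arm totals: 243 at 0.4 and 162 at 0.6. The printed 204 is therefore a total for the omnibus test at rho=0.5, and 204×1.35 = 275.4 gives 276. The per-group label and the way dropout is added are separate matters.

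**2. What f=0.1 means between arms.** f = √(mean of squared interaction cell effects), in SD of a single measurement. Let D be the largest arm difference at t3.

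| Arms | Time course | f | D for f=0.1 |
|---|---|---|---|
| equally spaced (0, ½, 1) | linear | 0.167·D | 0.60 |
| equally spaced | from t2 on, or t3 only | 0.192·D | 0.52 |
| one arm apart (0, 0, 1) | linear | 0.192·D | 0.52 |
| one arm apart | from t2 on, or t3 only | 0.222·D | 0.45 |

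The hypothesised order is therapist, then computer, then CAU. With equal spacing, D is 0.52–0.60 SD and each neighbouring pair differs by half of that, 0.26–0.30 SD. The 0.45 needs two arms to be equal, which the hypotheses do not expect.

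**3. Pairwise power if f=0.1 is true.** 92×0.65 = 59.8, about 60 per arm. SE unadjusted = √(2/60) = 0.183; baseline-adjusted at rho=0.5 = √(2/60×0.75) = 0.158. Power ≈ Φ(difference/SE − 1.96).

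| Contrast | Difference | Unadjusted | Adjusted |
|---|---|---|---|
| therapist vs computer, computer vs CAU | 0.26 | 30% | 38% |
| the same | 0.30 | 38% | 48% |
| therapist vs CAU | 0.52 | 81% | 91% |
| therapist vs CAU | 0.60 | 91% | 97% |

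**4. Pairwise power if therapist and computer differ by d=0.2.**

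| Analysed per arm | Unadjusted | Adjusted, rho 0.5 | Adjusted, rho 0.7 |
|---|---|---|---|
| 60 | 19% | 24% (0.20/0.158 = 1.26) | 34% |
| 92 (no dropout) | 27% | 35% | 48% |

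**5. Detectable difference at 80% power**, baseline-adjusted, rho=0.5: 2.80×0.158 = 0.44 SD at 60 per arm; 2.80×0.128 = 0.36 SD at 92 per arm. Unadjusted at 60 per arm: 2.80×0.183 = 0.51 SD.

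**The case against.** Powering on a group-by-time interaction is common, and the article says openly that it does so. The pairwise figures depend on inputs that the protocol does not give. Treating 60 per arm as the whole sample is somewhat pessimistic, because the planned mixed models also use t1 and t2 data from people missing at t3. All of this stands, and it is why ranges are given. The no-dropout row bounds what a mixed model could recover, and at d=0.2 nothing in the grid exceeds 48%.

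Four stronger readings are tempting but not supported.

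- *Therapist versus computer is the question the trial can answer least.* With equally spaced arms, computer versus CAU has the same difference and the same 30–48% power.
- *Power for this contrast is 24%.* That is one cell of a grid resting on d=0.2, rho=0.5 and 60 analysed per arm.
- *The protocol's own evidence shows the planned effect to be inflated.* The Background reports g=0.18 and 0.27 in students ("They found small intervention effects for depression"), but these pool guided and unguided programmes and are not the source used for sizing. It also cites a meta-analysis that "found no difference between personal or no personal guidance", yet the same sentence says that guided programmes generally report larger effects. What the sizing source reports, and how f=0.1 was taken from it, cannot be seen here.
- *The trial will read a null result as showing that feedback is unnecessary.* No section plans this. The Discussion says only that the study will add to understanding of the need for individualised feedback.

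**Conclusion.** The mismatch is real: the 80% belongs to the omnibus interaction, while the hypotheses are pairwise and have no stated power. Under the protocol's own f=0.1, with the hypothesised order and equal spacing, therapist versus CAU is adequately covered (about 81–97%), but the two neighbouring contrasts are not (roughly 30–48%), all at about 60 analysed per arm. At an assumed d=0.2, therapist versus computer has about 19–35% power over 60–92 per arm (unadjusted to adjusted at rho=0.5), and at most about 48% with rho=0.7 and no dropout. Of the assumptions, rho=0.5 is well supported because it returns the printed 204. Equal spacing, d=0.2 and the number analysed are assumptions, and they move the size of the shortfall, not its direction. The design itself need not change. The power statement should be corrected, at should-fix rather than must-fix level.

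**What to change.** Keep N at 276 and revise the Sample size calculation section:

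1. State that the 80% refers to the omnibus interaction only, and that f=0.1 corresponds to about 0.52–0.60 SD between the extreme arms under the hypothesised order with equal spacing (0.45 SD at the lowest, if two arms are equal).
2. Add the detectable difference per contrast at t3: about 0.44 SD at 60 per arm and 0.36 SD with no dropout, naming the assumptions (80% power, two-sided 0.05, baseline-adjusted, rho=0.5).
3. State that therapist versus computer will be reported as an estimate with its 95% CI and that non-significance will not be taken as equivalence.
4. In the closing paragraph of the Discussion, do not use the large sample as support for that contrast.

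The cost is protocol wording. The downside is that the stated sensitivity becomes less favourable.

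### The sample size section calls a plain 0.05 a corrected alpha, yet with two primary outcomes each tested at 0.05 the family-wise error is about 8 to 9%

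*Protocol article*

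**What the plan says.** The Sample size calculation section bases the power on the "mixed factors 3×3 interaction difference between the three treatment arms and three time points". It gives the effect size ("We anticipate a small interaction effect (Cohen’s f=0.1) at post-treatment"), the power ("We determined a statistical power (1-ß) of.8") and a "corrected alpha of α=0.05". The result is worded as "With a two-tailed hypothesis, we need 204 participants per intervention group". A dropout rate of 35% then leads to 276 in total, 92 per arm.

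Under Primary outcomes, the GAD-7 and the PHQ-9 "are the primary outcomes in the study and assess respectively" anxiety and depressive symptoms. The Background section states three pairwise hypotheses. The first two are that the therapist-guided and computer-guided "conditions are both significantly more effective than CAU"; the third is that therapist guidance is superior to computer guidance.

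The article does not say what was corrected, by what method or for how many tests. It also does not say whether one primary outcome is enough for success or both are needed, or how the pairwise hypotheses relate to the interaction test. No correlation between repeated measures is given.

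**The concern.** A correction for multiple testing normally leaves a per-test level below 0.05. A two-outcome Bonferroni correction, for example, gives 0.025. Here the level that fixed the sample size is 0.05 itself, so the adjective and the number do not fit together.

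This is different from leaving a multiplicity procedure to an analysis plan. The alpha behind the sample size is stated in this article and described as already adjusted. If the trial later reports a significant effect on one of the two outcomes, a reader would rely on this sentence to believe that multiplicity had been handled. If 0.05 was in fact the per-test level, that belief would be wrong. If a lower level is applied at analysis, the trial would have less power than stated, unless the repeated measures correlate more strongly than 0.5.

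**Working it through.** **Inputs from the article:** 3 arms (k = 3), 3 time points (m = 3), f = 0.1, power 0.80, alpha 0.05, dropout 35%, total 276, two primary outcomes, three pairwise hypotheses. The two-tailed specification has no effect on an omnibus F test.

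**Assumptions, not in the article:** correlation between repeated measures rho = 0.5 unless stated otherwise; sphericity; 204 read as a total. The last reading is needed because 276 in total follows from 204 × 1.35 = 275.4, rounded up, and because 3 × 204 = 612 would give power above 99.9%.

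**Step 1. Reproduce 204.** For the within-between interaction, lambda = f² × N × m / (1 − rho), df1 = (k − 1)(m − 1) = 4 and df2 = (N − k)(m − 1).

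- N = 204: lambda = 0.01 × 204 × 3 / 0.5 = 12.24 and df2 = 201 × 2 = 402. Power at alpha 0.05 is 80.6%.
- N = 201: power is 79.9%.

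So 204 is the smallest multiple of three that reaches 80% at an unadjusted 0.05.

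**Step 2. Same calculation at 0.025 (two outcomes), rho = 0.5.**

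| Analysable N | Power at 0.05 | Power at 0.025 |
|---|---|---|
| 204 | 80.6% | 72.0% |
| 179 (276 × 0.65 = 179.4) | 74.4% | 64.6% |

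The loss is 8.6 points at 204 and 9.8 points at 179. To reach 80% at 0.025, 238 analysable participants are needed (240 with equal arms).

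**Step 3. Sensitivity to rho.** At alpha 0.025, the N for 80% power (multiples of three) is 285 at rho 0.4, 240 at 0.5, 216 at 0.55 and 192 at 0.6. At rho of about 0.575, N = 204 gives 80% power at 0.025.

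**Step 4. Family-wise error if both outcomes are null.** If each outcome has one omnibus test at 0.05 and the outcomes are independent, the error is 1 − 0.95² = 9.75%. If they are perfectly correlated, it is 5%. Values in between come from simulation (1,000,000 draws, large-sample three-arm test, outcome correlation r). The ungated column takes all three pairwise contrasts per outcome at |z| > 1.96, with shared arms.

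| r | Two omnibus tests at 0.05 | Six pairwise tests, ungated at 0.05 |
|---|---|---|
| 0 | 9.8% | 22.9% |
| 0.5 | 9.2% | 21.3% |
| 0.6 | 8.8% | 20.6% |
| 0.7 | 8.5% | 19.6% |
| 1 | 5.0% | 12.3% |

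If pairwise tests follow only a significant omnibus test for that outcome, the error under this null is the same as in the omnibus column.

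**Step 5. Check of a simple Holm rule.** Suppose 0.05 were released to the second outcome as soon as the first outcome's omnibus test is significant at 0.025. Let one arm truly differ on the first outcome, so that this happens almost always. One true pairwise null on the first outcome remains at 0.025, and the second outcome is tested at 0.05. With independent outcomes the error is 1 − 0.975 × 0.95 = 7.4%, and simulation gives about 7%. That rule does not hold 5%.

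**The case against.** The strongest reply is that this is a condensed article. The correction may be described in a full protocol or analysis plan that is not shown, and 0.05 may be meant as the overall level after correction. That stands to this extent: the absence of a named procedure is no fault in itself, and the article does not prove that no correction will be made. It does not rescue the sentence, because 0.05 is given as the level used to obtain the sample size.

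Two stronger readings are tempting, and the article supports neither.

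- A reader might infer that 204 can arise only from an uncorrected 0.05. The article gives no rho, and 204 also gives 80% power at 0.025 with rho of about 0.575. The exact match at the round value 0.5 makes an uncorrected 0.05 the simplest explanation, but not the only possible one.
- A reader might infer six unadjusted primary tests and a family-wise error of about 20%. Two outcomes and three hypotheses do give six comparisons, but no section says that they will be tested ungated at 0.05, or that success on any one of them would count. The design is powered on the interaction, and the hypothesis on the two iCBT arms against care as usual is worded jointly. The article neither states nor excludes ungated testing, so 12 to 23% is what could happen, not what is planned.

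It is also fair to say that if both outcomes must succeed, no adjustment across them is needed. The article does not say that this is the rule.

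**Conclusion.** The point holds in a limited form. The article describes as corrected a level that is numerically the unadjusted one, and its sample size matches that unadjusted level exactly at rho = 0.5 with sphericity and 204 taken as a total. For the two interaction tests that the design is powered on, the family-wise error is about 8 to 9% at an assumed outcome correlation of 0.5 to 0.7, with outer limits of 5 and 10%. This assumes that success on either outcome counts. The higher range of 12 to 23% applies only if the pairwise hypotheses are tested without a gate. The power shortfall at 0.025 depends on rho: it is real at 0.5 and disappears at about 0.575.

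**What to change.** State which of two rules applies, and make the alpha sentence match it.

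1. **Either outcome can carry the claim.** Test each primary outcome's interaction at 0.025. Test that outcome's three pairwise contrasts at 0.025 only if its interaction is significant; with three arms this gate is a closed test. Pass alpha on to the other outcome only if all contrasts of the first are rejected. Restate the power at 0.025 together with the rho used.
2. **Both outcomes are required.** Say so, keep 0.05, delete the word *corrected*, and state that joint power is lower than the power for each outcome.

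The cost is wording in the protocol and analysis plan. Under the first rule, the stated power per outcome falls by about 9 to 10 points at rho = 0.5. Keeping 80% there would need 238 analysable participants instead of 204. If a rho of about 0.575 or more can be justified, 204 analysable participants remain enough.

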**Methods and analysis:**

University students with anxiety and/or depressive symptoms will be randomised to a (1) 7-week iCBT programme (excluding booster session) with therapist feedback, (2) the identical iCBT programme with computer feedback only or (3) care as usual. Participants in the care as usual condition are informed and referred to conventional care services and encouraged to seek the help they need. Primary outcome variables are self-reported levels of anxiety as measured with the General Anxiety Disorder-7 and self-reported levels of depression as measured with the Patient Health Questionnaire-9. Secondary outcomes include treatment adherence, client satisfaction, medical service use, substance use, quality of life and academic achievement. Assessments will take place at baseline (t1), midtreatment (t2), post-treatment (t3), at 6 months (t4) and 12 months (t5) postbaseline. Social anxiety and perfectionism are included as potentially important predictors of treatment outcome. Power calculations are based on a 3 (group) × 3 (measurement: pretreatment, midtreatment and post-treatment) interaction, resulting in an aimed sample of 276 participants. Data will be analysed based on intention-to-treat and per protocol samples using mixed linear models.

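### The sample-size section labels 204 as a per-group requirement, but it is the three-arm total (68 per group), and 276 enrolled does not deliver 204 completers at 35% dropout

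*Protocol article*

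**What the plan says.** Under Sample size calculation, the protocol article bases power on the group-by-time interaction: "The power analysis is based on the mixed factors 3×3 interaction difference between the three treatment arms and three time points". The assumed effect is Cohen's f = 0.1 ("We anticipate a small interaction effect (Cohen’s f=0.1) at post-treatment"), with "statistical power (1-ß) of.8 and corrected alpha of α=0.05". It concludes that "we need 204 participants per intervention group to be able to detect a statistically significant result".

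The same paragraph then applies a 35% dropout rate and gives a minimum total of 276 at 1:1:1, "with 92 participants in each group". The abstract repeats the total: "resulting in an aimed sample of 276 participants". Neither place gives a within-person correlation or a sphericity value.

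**The concern.** An allowance for dropout can only raise a requirement. Here a stated need of 204 per group becomes 92 per group once the allowance is made. Reading the phrase as covering only the two iCBT arms does not help: that is already 2 × 204 = 408 before dropout, and the paragraph fixes 92 in every arm.

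This paragraph is the reference against which recruitment and achieved power will be judged. As printed, it does not say which number governs. Once the label is corrected, a second gap shows: the paragraph does not say how many completers 276 is expected to yield, and the answer is fewer than 204.

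**Working it through.** **Inputs from the protocol article:** k = 3 groups, m = 3 time points, f = 0.1, alpha = 0.05, power 0.80, dropout 35%, total 276, 92 per group. **Inputs not given, so assumed:** within-person correlation ρ = 0.5 and sphericity (ε = 1).

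**1. Reproduce the plan's dropout step (needs no assumed input).**
- 204 taken as the total: 204 × 1.35 = 275.4, rounded up to 276. Per arm: 204 / 3 = 68, and 68 × 1.35 = 91.8, rounded up to 92. Both printed figures come out.
- 204 taken as per group: 3 × 204 = 612. Then 612 × 1.35 = 826.2, rounded up to 827, or 612 / 0.65 = 941.5, rounded up to 942. Neither is 276.

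**2. Reproduce the 204.** Noncentral F for the within-between interaction:
- λ = f² · N · m / (1 − ρ)
- df1 = (k − 1)(m − 1) = 4
- df2 = (N − k)(m − 1)

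At N = 204, λ = 0.01 × 204 × 3 / 0.5 = 12.24 and df2 = 201 × 2 = 402.

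| Total N | Power (ρ = 0.5, ε = 1) |
|---|---|
| 179 | 0.744 |
| 201 | 0.799 |
| 204 | 0.806 |
| 276 | 0.919 |
| 612 | 0.9995 |

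The smallest total reaching 0.80 is 202, and the smallest that splits into three equal arms is 204. A total of 612 would give power far above the stated 0.8.

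**3. Sensitivity to the unstated correlation (ε = 1).**

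| ρ | Total N for power 0.80 |
|---|---|
| 0.3 | 281 |
| 0.4 | 242 |
| 0.5 | 202 |
| 0.6 | 162 |
| 0.7 | 122 |

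Under sphericity even ρ = −0.5, the lower limit for three equally correlated measurements, needs only 600 in equal arms. Departures from sphericity raise the number: at ρ = 0.5 the total in equal arms is 237 for ε = 0.8 and 327 for ε = 0.5. The match at 204 therefore supports reading it as the total, but does not prove which inputs were used.

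**4. What 276 delivers.**
- Completers expected: 276 × 0.65 = 179.4, about 179. Per group: 92 × 0.65 = 59.8, about 60.
- Power at 179 on the assumptions of step 2: about 0.74.
- Enrolment that leaves 204 completers: 204 / 0.65 = 313.8, rounded up to 314, or 315 (105 per arm) for equal arms.

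**The case against.** The strongest reply is that this is a wrong label on an intermediate figure. The number the trial recruits to, 276 at 92 per group, is the same in the abstract and in the sample-size section, and a careful reader can recover the meaning of 204 from the dropout step. That stands: the label by itself changes no recruitment target, allocation, endpoint or analysis.

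A reader might instead infer that the trial really needs 612 completers and is enrolling less than half of its requirement (276 / 612 = 45%). The document does not support that. Its own dropout arithmetic works only with 204 as the total, and 612 would give power near 1 on the assumptions in the working, not 0.8.

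It is also fair to say that a journal article commonly leaves the correlation and sphericity inputs to the full protocol or analysis plan. Their absence is not a fault in itself, and 0.5 is my back-solved value, not the sponsor's.

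Finally, the planned mixed linear models can use the partial data of those who drop out. The 0.74 treats dropouts as contributing nothing, which is also the convention behind the plan's dropout allowance; realised power could be higher. This softens the power figure but does not make the multiplication by 1.35 the right step for securing 204 completers.

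**Conclusion.** The concern holds as a correction of the stated requirement and of the power that goes with 276. The per-group label on 204 is wrong by a factor of three: 204 is the total, 68 per group. That conclusion rests on the document's own arithmetic; the power calculation supports it if ρ = 0.5 and sphericity holds.

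With the label corrected, the planned 276 still falls short of its stated aim. At 35% dropout it leaves about 179 completers against 204, a gap of about 25, and power of about 0.74 against 0.80. The power figure depends on the assumed correlation and sphericity and on counting completers only. The completer shortfall depends only on the 35% rate and on 204 being the required number of completers.

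**What to change.** In the sample-size section:

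1. Relabel 204 as the total for the three arms, 68 per group.
2. Confirm and report the correlation and sphericity inputs actually used. Do not insert 0.5 unless it was the value entered.
3. Restate what 276 delivers: about 179 completers (about 60 per group) at 35% dropout, with the power that follows from the confirmed inputs (about 0.74 on the assumptions used here). If 204 completers remain the aim, state that dividing by 0.65 gives 314 enrolled, or 315 for equal arms.

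Items 1 and 2 cost one sentence of text each. Restating the power in item 3 also costs only text. Raising enrolment from 276 to 315 would mean 39 more participants, which is the sponsor's choice and not a consequence of the label error.
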